### Hypotheses

The primary hypotheses describe the comparisons of the primary endpoints for the three different analgesic regimens:1$$\begin{array}{ccc}{\mathrm{H}}_{1}:& {h}_{01}: {\mathrm{m}}_{\mathrm{met}}-{\mathrm{m}}_{\mathrm{fen }}\le {\updelta }_{\mathrm{I}}, & {h}_{\mathrm{a}1}: {\mathrm{m}}_{\mathrm{met}}-{\mathrm{m}}_{\mathrm{fen}}> {\updelta }_{\mathrm{I}}\\ {\mathrm{H}}_{2}:& {h}_{02}:{\mathrm{m}}_{\mathrm{met}}-{\mathrm{m}}_{\mathrm{mor}} \le {\updelta }_{\mathrm{I}},& {h}_{\mathrm{a}2}: {\mathrm{m}}_{\mathrm{met}}-{\mathrm{m}}_{\mathrm{mor}}> {\updelta }_{\mathrm{I}}\\ {\mathrm{H}}_{3}:& {h}_{03}:{\mathrm{m}}_{\mathrm{fen}}-{\mathrm{m}}_{\mathrm{mo}}\mathrm{r }\le {\updelta }_{\mathrm{I}},& {h}_{\mathrm{a}3}: {\mathrm{m}}_{\mathrm{fen}}-{\mathrm{m}}_{\mathrm{mor}}> {\updelta }_{\mathrm{I}}\end{array}$$where *m*_x_ is the mean reduction in NRS for treatment *x* and $${\delta }_{I}$$ is the non-inferiority margin.

*Null hypothesis h*_*01*_*:* methoxyflurane regimen is inferior to IN fentanyl regimen.

*Null hypothesis *$${h}_{02}$$*:* methoxyflurane regimen is inferior to IV morphine regimen.

*Null hypothesis *$${h}_{03}$$*:* IN fentanyl regimen is inferior to the IV morphine regimen.

*Alternative hypothesis *$${h}_{a1}$$*:* methoxyflurane regimen is non-inferior to IN fentanyl regimen.

*Alternative hypothesis *$${h}_{a2}$$*:* methoxyflurane regimen is non-inferior to IV morphine regimen.

Alternative hypothesis $${h}_{a3}$$: IN fentanyl regimen is non-inferior to IV morphine regimen.

### Sample size

The sample size with $$\alpha$$ = 0.05 and $$\beta$$ = 0.10 (90% power) was estimated using a two-sided *t*-test [11, 21, 22]. Expected pain reduction after 10 min was set to 3.77 for methoxyflurane, 2.54 for fentanyl, and 2.70 for morphine treatment regimen based on similar studies [11, 19, 20]. A common conservative standard variation of 2.20 was used. Non-inferiority margin is set to $${\delta }_{I}$$ = 1.3 based on [22, 23]. Sample size required to detect this difference 10 min after administration of IMP was estimated to be *n* = 88 in each arm. That gives a total number of participants of 264, and the plan is to include 3 × 90 = 270 patients per protocol allowing for two dropouts in each group, in total six dropouts, of the per-protocol population without losing power for the calculations of the primary endpoint.

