**Method/design:**

The PreMeFen study is a phase three, three-armed, randomized, controlled, non-inferiority trial to compare three regimens of analgesics: inhalation of methoxyflurane and intranasal (IN) fentanyl versus IV morphine. It is an open-label trial with a 1:1:1 randomization to the three treatment groups. The primary endpoint is the change in pain numeric rating scale (NRS) (0–10) from baseline to 10 min after start of investigational medicinal product administration (IMP). The non-inferiority margin was set to 1.3, and a sample size of 270 patients per protocol (90 in each treatment arm) will detect this difference with 90% power.

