## Background

Pre-hospital underuse of analgesics (oligoanalgesia) remains a global health problem [1–4]. Between 35 and 53% of patients describe moderate to severe pain during pre-hospital management [5], and pain management is considered a primary task for emergency medical service (EMS) providers [6, 7]. Still, barriers to adequate analgesia include challenging environment, lack of competence, and experience [8]. Although pre-hospital pain management often involves IV opioid administration [9], cannulation has been described to fail in 12–26% of adults [10], leading to a potential delay in administration of analgesia. Patients may benefit from a more easy-to-administer analgetic, which should be delivered safely, effectively, non-invasively and should be fast-acting. Reviews suggest two such alternatives: IN fentanyl, a synthetic opioid [8], and inhaled low-dose methoxyflurane, a volatile anesthetic from a group of fluorinated hydrocarbons [11]. Methoxyflurane in low dose is a non-narcotic analgesic widely used in Australia and New Zealand [11]. The slightly volatile gas is administered as a liquid via an inhalation chamber in a whistle-like pipe, while the exhaled air is filtered in a coal chamber on the same whistle [12].

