## Methods

### Study design

We applied the Norwegian Clinical Research Infrastructure Network (NorCRIN) templates [18] to design a randomized, controlled, open-label, three-arm, non-inferiority, phase three drug trial. The trial will be performed according to the principles of the Helsinki Declaration. The randomization is 1:1:1 to the three treatment groups, with 90 patients in each group, totaling 270 patients. Patients in all treatment groups follow a treatment regime rather than receiving a single drug dose. For ethical reasons, a placebo arm was excluded. The study protocol was drafted in accordance with the Standard Protocol Items: Recommendations for Interventional Trial guidelines (SPIRIT) [19].

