**Fig. 2 Fig2:**
[figure not shown]
Non-inferiority chart. The lines A–D represent mean and confidence interval of the differences in NRS-changes in the two treatment groups a and b. Examples A and B show that the agent a is inferior to agent b, while examples C and D confirm that agent a is non-inferior to agent b. IMP, investigational medicinal product; NRS, numeric rating scale

$${H}_{1}\to {H}_{2}\to {H}_{3}$$

The statistical chain of testing and decisions will be:*Test *$${H}_{1}$$*:* If part of the 95% confidence interval is below non-inferiority margin, we stop testing without any conclusion on efficacy. If the 95% confidence interval is above the non-inferiority margin, then we claim non-inferiority of methoxyflurane vs fentanyl and proceed with testing $${H}_{2}$$.*Test *$${H}_{2}$$*:* If part of the 95% confidence interval is below the non-inferiority margin, we stop testing without any further conclusion on efficacy. If the 95% confidence interval is above the non-inferiority margin, then we claim non-inferiority of methoxyflurane vs morphine and proceed with testing $${H}_{3}$$.*Test *$${H}_{3}$$*:* If part of the 95% confidence interval is below the non-inferiority margin, we stop testing without any further conclusion on efficacy. If the 95% confidence interval is above the non-inferiority margin, then we claim non-inferiority of fentanyl vs morphine.

The nominal significance level is set to 5%, and the non-inferiority margin is set to 1.3. Non-inferiority is determined based on a 1-sided equivalence *t*-test on the per protocol population and confirmed, for sensitivity reasons, on the modified intention to treat population.

We plan to compare the incidence of serious and non-serious adverse events between the groups using a chi-squared test or a Fisher exact test if necessary (expected frequency less than 5). We will summarize patient satisfaction and medical personnel view on practicality.

Demographic and baseline information of the three study groups will be compared using *t*-tests (means), Mann–Whitney *U* (medians), and chi-square (proportions) tests. If there are any significant differences, linear regression will be performed to adjust for significantly different covariates. No interim analysis will be performed.

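### The 88 per arm does not follow from the stated non-inferiority inputs, and 270 is the number randomised in one place and the number per protocol in others

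*Protocol article*

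**What the plan says.** The Sample size section sets alpha at 0.05 and says that the calculation, with beta "0.10 (90% power) was estimated using a two-sided *t*-test". It gives expected reductions at 10 minutes of 3.77 (methoxyflurane), 2.54 (fentanyl) and 2.70 (morphine), a common SD of 2.20 and a non-inferiority margin of 1.3. It continues: "Sample size required to detect this difference 10 min after administration of IMP was estimated to be" 88 per arm, 264 in all. This is raised to 3 × 90 = 270 per protocol, "allowing for two dropouts in each group, in total six dropouts, of the per-protocol population without losing power".

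The Abstract (Method/design) ties the number to the margin: "a sample size of 270 patients per protocol (90 in each treatment arm) will detect this difference with 90% power".

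Study design describes 1:1:1 randomisation "with 90 patients in each group, totaling 270 patients".

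The Statistics section declares non-inferiority when the 95% confidence interval lies wholly on the favourable side of the margin. It tests H1, H2 and H3 in fixed sequence, each at full alpha, and also refers to a one-sided test on the per-protocol population: "The nominal significance level is set to 5%, and the non-inferiority margin is set to 1.3". Under Rescue medication, a patient given rescue before the 10-minute assessment is removed from the per-protocol analysis.

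**The concern.** The number per arm and the 90% power are headline design figures and appear in the Abstract. A reader should be able to reproduce them from the inputs printed beside them, and cannot. The sentence giving 88 speaks of detecting a difference, and the section names a two-sided t-test. That is the language of a superiority calculation, whereas the analysis is a non-inferiority test. The reader therefore cannot tell which comparison, which assumed true difference or which alpha the 90% refers to.

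The second problem is what 270 counts. The per-protocol set is the primary analysis set. If 270 are randomised, every exclusion reduces that set below 270. If 270 are to be per protocol, more than 270 must be randomised. The two readings give different recruitment targets and different room for losses.

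**Working it through.** **Inputs.** From Sample size: margin 1.3, SD 2.20, power 90%, alpha 0.05, reductions 3.77 / 2.54 / 2.70. From Statistics: a 95% confidence interval rule, equivalent to one-sided 0.025, alongside a one-sided test at a nominal 5%. Both alphas are therefore run. The margin is taken as a boundary of −1.3 for the new minus the reference regimen, which is what the worded hypotheses describe.

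**Expected differences.** H1: 3.77 − 2.54 = +1.23. H2: 3.77 − 2.70 = +1.07. H3: 2.54 − 2.70 = −0.16.

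**Formula.** Per-arm n = 2 × (z for alpha + z for power)² × SD² / d², where d is 1.3 plus the assumed true difference. At one-sided 0.025 the numerator is 2 × (1.960 + 1.282)² × 2.20² ≈ 101.7. At one-sided 0.05 it is 2 × (1.645 + 1.282)² × 2.20² ≈ 82.9. The columns marked t use exact noncentral t power.

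| Case | d | n at 0.025, normal | t | n at 0.05, normal | t |
|---|---|---|---|---|---|
| True difference 0 | 1.30 | 60.2 | 62 | 49.1 | 50 |
| H1 | 2.53 | 15.9 | 17 | 13.0 | 14 |
| H2 | 2.37 | 18.1 | 20 | 14.8 | 16 |
| H3 | 1.14 | 78.3 | 80 | 63.8 | 65 |

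**Attempt to reproduce 88.** No row gives it. With a true difference of zero, 88 would need an SD of about 2.65 instead of 2.20. Figures at or near 88 arise from calculations that the article does not describe:

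- Two-sided 5% superiority of methoxyflurane over morphine, d = 1.07: 101.7 / 1.07² = 88.8, so 89 (normal) or 90 (t).
- H3 at one-sided 0.05/3, d = 1.14: 86.6, so 88 (t). The plan uses a fixed sequence with no split of alpha.
- Superiority on 1.23 at two-sided 0.05/3: 86.4, so 88 (t).
- H3 at one-sided 0.025 with an unstated 10% inflation: 80 × 1.10 = 88.

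**Power actually provided at one-sided 0.025 (exact t).** With 88 per arm: 97.4% at zero difference, 92.8% for H3, over 99.9% for H1 and H2. With 90 per arm: 97.6% at zero difference and 93.3% for H3.

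**The 270.** 90 − 2 = 88 is correct arithmetic, and 2/90 = 2.2%. If 270 is the number randomised, that 2.2% has to cover every per-protocol exclusion, including rescue before 10 minutes. The article gives no exclusion rate. The rates below are assumptions, applied equally to all arms:

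| Assumed exclusion | Per protocol from 90 randomised (rounded down) | H3 power | Randomised per arm to keep 88 | Randomised per arm to keep 90 |
|---|---|---|---|---|
| 5% | 85 | 91.9% | 93 | 95 |
| 10% | 81 | 90.6% | 98 | 100 |
| 20% | 72 | 87.0% | 110 | 113 |

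At 72 per arm, power at zero true difference is still 94.1%.

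**The case against.** The strongest reply is that the discrepancy is on the safe side. This stands. 88 exceeds every non-inferiority requirement in the first table, the promised 90% is met for all three comparisons, and no test or decision rule changes.

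It can also be said that the Sample size section is coherent when read alone: 90 per-protocol patients per arm, of whom 88 are needed. The Study design sentence is condensed and does not exclude recruiting beyond 270. That makes the conflict milder but does not remove it, because that sentence attaches 270 to the randomisation. The Missing data section also plans imputation for the primary endpoint, so a missing score need not be a lost patient. Imputation does not restore a patient excluded from the per-protocol set for early rescue.

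Three stronger readings are tempting, and the documents support none of them:

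- **That 88 is a superiority calculation in disguise.** The wording fits, but that route gives 89 or 90, and several other routes give exactly 88. The origin cannot be inferred.
- **That the trial is too small.** The power figures show the reverse.
- **That the morphine arm will be depleted.** The Background says "cannulation has been described to fail in 12–26% of adults", and morphine is the only intravenous regimen. Turning this into lost patients assumes that the range applies after all attempts and that every such patient leaves the per-protocol set. The article says neither. On both assumptions 67 to 79 of 90 morphine patients remain, and H3 power against 90 fentanyl patients is 89.1% to 91.7%, close to the target.

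**Conclusion.** The point holds as an error in stated figures, not as a shortfall in patients. On the printed inputs the non-inferiority design needs 62 per arm at zero difference, or 80 for its weakest comparison, under the 95% confidence interval rule. Under one-sided 0.05 it needs 50 or 65. The stated 88 with 90% power is neither. Its actual power under the confidence interval rule is 92.8% for H3 and higher elsewhere.

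The two meanings of 270 are a separate contradiction. The claim that two losses per arm cost no power is tied to an 88 that the design does not require: H3 power stays at or above 90% down to 80 per arm, but falls to 87.0% at 72.

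These results assume the stated SD and expected reductions, equal arm sizes and an unadjusted two-sample comparison.

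A clerical matter sits beside this. The expected reductions are "based on similar studies [11, 19, 20", but Study design uses reference 19 for the SPIRIT guideline and Interventions uses reference 20 for the Glasgow coma scale. This is a numbering slip and does not show that the values are wrong.

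**What to change.** 1. Restate the sample size as a non-inferiority calculation that names the comparison, the assumed true difference, alpha and sidedness, aligned with the 95% confidence interval rule. At one-sided 0.025, with SD 2.20 and margin 1.3, 80 evaluable patients per arm give 90% power for H3, 88 give 92.8% and 90 give 93.3%. Alternatively, disclose the different inputs that produced 88. Recruitment began in November 2021, so a new derivation should be labelled as a restatement and not presented as the original basis.
2. Reconcile the two-sided t-test in Sample size with the one-sided test at a nominal 5% and the 95% confidence interval in Statistics.
3. State whether 270 is the number randomised or the number per protocol, and make the Abstract, Study design and Sample size agree. The sponsor must say which; the article does not settle it.
4. Replace the two-dropouts statement with H3 power over a range of per-protocol sizes. Include any cannulation-loss scenario only as a labelled assumption.
5. Correct the reference numbers for the expected reductions.

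The cost is a rewritten paragraph and consistent wording in three places. Restating the figures needs no extra patients. If 270 is meant as the per-protocol number, the number randomised must be stated as larger.

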### Statistics

The hypotheses in Eq. (1) will be tested and a conclusion of non-inferiority will be made if the 95% CI of estimated treatment difference fully lie above the inferiority margin; see Fig. 2. Hypotheses $${H}_{1}$$, $${H}_{2}$$, and $${H}_{3}$$ will be tested using the fixed-sequence procedure, to avoid inflating the significant level for the overall test. Accordingly, family-wise error rate will remain the same as the local nominal significance level *a*. The test will be performed in the following order:

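### Eq. (1) and the confidence-interval rule lack a minus sign before the margin, so as printed H1 to H3 test superiority by more than 1.3 points instead of non-inferiority

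*Protocol article*

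**What the plan says.** All references are to the protocol article.

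- **Scale (Methods, Hypotheses).** m_x "is the mean reduction in NRS for treatment" x, so a larger m means better pain relief.
- **Hypotheses (Eq. (1)).** For H1 the null is m_met − m_fen ≤ δ_I and the alternative is m_met − m_fen > δ_I. H2 (methoxyflurane against morphine) and H3 (fentanyl against morphine) have the same form. In words, the alternative of H1 is that the "methoxyflurane regimen is non-inferior to IN fentanyl regimen".
- **Margin.** Sample size sets the symbol δ_I equal to 1.3. Statistics says "the non-inferiority margin is set to 1.3" once, after the decision chain. The Abstract and the Discussion also give 1.3 without a minus sign.
- **Decision rule (Statistics).** The rule is that "a conclusion of non-inferiority will be made if the 95% CI of estimated treatment difference fully lie above the inferiority margin". For H1: "If part of the 95% confidence interval is below non-inferiority margin, we stop testing without any conclusion on efficacy". H2 and H3 follow only if the preceding step succeeds, and Limitations says that later tests would otherwise be exploratory.

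**The concern.** When a larger value is better, non-inferiority means that the new regimen is not worse by more than the margin, so the alternative is a difference above −1.3. Substituting δ_I = 1.3 into the printed alternative gives a difference above +1.3, which is superiority by more than the margin. Two regimens with identical effect would fail it.

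This is the primary decision rule, and H1 is the first step of a fixed sequence. If the rule were followed as printed, failure at H1 would also remove both morphine comparisons from confirmatory testing. If the sign is instead changed without comment at analysis, the hypothesis tested is not the one published. In an open-label trial, that is an avoidable weakness in the pre-specification.

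**Working it through.** **Inputs, all from the article.** "Expected pain reduction after 10 min was set to 3.77 for methoxyflurane, 2.54 for fentanyl, and 2.70 for morphine treatment regimen"; "A common conservative standard variation of 2.20 was used"; 90 patients per arm; a 95% confidence interval and, in the same section, a one-sided t-test at a nominal 5%.

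Planned differences in mean reduction:
- H1: 3.77 − 2.54 = 1.23
- H2: 3.77 − 2.70 = 1.07
- H3: 2.54 − 2.70 = −0.16

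**1. The plan's own figure.** Sample size gives 88 per arm. A two-sided 5% test of zero difference with 90% power and a difference of 1.07 needs 2 × (2.20 × (1.960 + 1.282)/1.07)² = 88.84, that is 89 per arm, which comes within one of the stated figure. Taking 1.3 as the margin with a true difference of 0 needs 2 × (2.20 × 3.242/1.3)² = 60.2, that is 61 per arm. The sample size therefore does not show which sign was used, and the sign problem does not depend on it.

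**2. Can another reading of m rescue the sign?** The Fig. 2 caption speaks of changes in NRS, so suppose m is the signed change, with negative values better. A difference above +1.3 would then mean that the new regimen is worse by more than 1.3 points. Neither reading yields non-inferiority.

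**3. Standard error.** SE = 2.20 × √(2/90) = 0.328.

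**4. Observed difference needed, using the 95% interval.**
- Margin +1.3: 1.3 + 1.96 × 0.328 = 1.94
- Margin −1.3: −1.3 + 1.96 × 0.328 = −0.66

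**5. Probability of passing a step.** P = Φ((Δ − M)/SE − z), where Δ is the true difference, M the margin, and z is 1.960 (95% interval) or 1.645 (one-sided 5%).

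- H1, M = +1.3, 95% interval: (1.23 − 1.3)/0.328 = −0.213; −0.213 − 1.960 = −2.173; P = 1.5%
- H1, M = +1.3, one-sided 5%: −0.213 − 1.645 = −1.858; P = 3.2%
- H3, M = −1.3, 95% interval: (−0.16 + 1.3)/0.328 = 3.476; 3.476 − 1.960 = 1.516; P = 93.5%

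The noncentral t distribution with 178 degrees of freedom gives nearly the same values:

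| Step | Δ | +1.3, 95% CI | +1.3, one-sided 5% | −1.3, 95% CI | −1.3, one-sided 5% |
|---|---|---|---|---|---|
| H1 | 1.23 | 1.5% | 3.2% | >99.9% | >99.9% |
| H2 | 1.07 | 0.4% | 1.0% | >99.9% | >99.9% |
| H3 | −0.16 | <0.01% | <0.01% | 93.3% | 96.5% |
| Arms equal | 0 | <0.01% | <0.01% | 97.6% | 98.9% |

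**6. The sequence.** In 400,000 simulated trials with 90 per arm and the 95% interval, the +1.3 rule passed H1 in 1.5% and both H1 and H2 in 0.09%; none passed all three. The −1.3 rule passed all three in 93.5%.

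**7. Why more patients would not help.** Since 1.23 is below 1.3, the printed null of H1 is true under the plan's own assumptions. At 90 per arm, 90% power at H1 under the literal rule would need a true advantage of 1.3 + 0.328 × (1.960 + 1.282) = 2.36 points.

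**The case against.** The intended direction is plain. Every null is called inferior and every alternative non-inferior. The design is described as non-inferiority throughout, and the Discussion derives 1.3 from the size of a clinically relevant difference, which is a magnitude. Quoting a margin as a positive number is ordinary practice, so the value 1.3 is not itself an error. The sentence with the decision rule also refers to Fig. 2, which may place the line at −1.3.

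Most of this stands, and it limits the point. A reader might infer that the trial is in fact set up to fail at H1, or that it is really a superiority trial. The article does not support either inference. The 1.5% describes literal application of the printed rule; with the evident intent, H1 passes almost surely. Nor would a literal failure at H1 be a finding of inferiority: the decision chain stops there without a conclusion on efficacy. A reader might also suspect a departure from a registered hypothesis, but only the published one can be judged here.

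The objection does not remove the defect. A positive magnitude is harmless when the hypothesis carries −δ_I, and Eq. (1) does not. Sample size ties that symbol to 1.3. A figure cannot override three formally stated hypotheses.

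**Conclusion.** The point holds as an error in the printed hypotheses and decision rule. With m as mean reduction and δ_I = 1.3, H1 to H3 require superiority by more than 1.3 points, against the article's own verbal hypotheses and design. No text in the article supplies the minus sign.

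The size is conditional on the rule being applied literally. Under the plan's means, an SD of 2.20 and 90 per arm, H1 then passes with probability of 1.5% (95% interval) or 3.2% (one-sided 5%), against more than 99.9% with −1.3. These figures assume approximately normal mean differences and a common SD. The sign error itself rests on none of those assumptions. It needs correcting because it fixes the threshold for the primary conclusion, although the intent is not in doubt.

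**What to change.** 1. Keep δ_I = 1.3 as a positive magnitude wherever it appears (Abstract, Sample size, Statistics, Discussion). Changing only some of these to −1.3 would create a new inconsistency.
2. In Eq. (1), write h0: m_x − m_y ≤ −δ_I against ha: m_x − m_y > −δ_I for H1, H2 and H3.
3. In Statistics, state that non-inferiority is concluded when the lower confidence limit for the difference in mean reduction exceeds −δ_I, that is −1.3. Use the same wording at each step of the chain.
4. Confirm that Fig. 2 plots the difference in mean reduction, new regimen minus comparator, with the line at −1.3.
5. Record the correction, with its date, before the treatment codes are revealed to the statistician. If the full protocol or the SAP already carries the negative sign, cite it.

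The cost is a wording change and a short dated note. It needs no further patients or data, and the planned 90 per arm stays as it is.
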